### 3) Measurement procedure – Comparison Group

: PCT physician/ : CRC or PCT nurse

|           |                                                    |                                                                                                                                                                                                                                                                                                                                                                                                                                 |
|-----------|----------------------------------------------------|---------------------------------------------------------------------------------------------------------------------------------------------------------------------------------------------------------------------------------------------------------------------------------------------------------------------------------------------------------------------------------------------------------------------------------|
| PROCEDURE | 1. Study registration and random assignment | Once patients are referred by the treating department to register for the early palliative care research, they are briefly informed of the study and asked to sign a written consent form . Upon completion of the Baseline Survey, random assignment is performed. Patients are provided with a copy of the early palliative care leaflet and patient educational materials (on cancer pain management) . |
|           | ▼                                                  |                                                                                                                                                                                                                                                                                                                                                                                                                                 |
|           | 2. Follow-up                                | At weeks 12, 18, and 24 surveys will be administered .
At follow-ups, the materials (on advance care planning and early palliative care) developed for the study are provided.                                                                                                                                                                                                                                 |

※ PCT team member roles may be modified in accordance with the situation at each institution.

#### **4) Statistical analysis**

- Main outcomes
  - The mean observed change from baseline and adjusted differences between change scores at 12, 18, and 24 weeks were analyzed based on the estimated regression model
  - Effect sizes were calculated as standardized mean differences (Cohen's d)
- Survival analysis
  - Two-year survival as the main survival outcome
  - Kaplan-Meier curves were used to compare the survival rates between the EPC and control groups two years after enrollment
  - To determine if the survival rate was higher in the group that received more interventions, participants were divided into groups with fewer than 10 interventions and more than 10 interventions
  - Patients who were alive at the time of the last follow-up (two years from the enrollment date) were censored on that date

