#### Inclusion Criteria:

1. Aged 20 or older.
2. Diagnosed with advanced solid tumor cancer (histologically/cytologically confirmed).
3. European Cooperative Oncology Group (ECOG) performance status: 0-2.
4. Estimated life expectancy of  $\leq 12$  months.
5. Consent to participate.

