## **Intervention**

1. Initial meeting with palliative care team within three weeks post-randomization.
2. Self-study materials/videos provided on early palliative care/advance care planning (SMASH-based).
3. Telephone coaching: Weekly for the initial 12 weeks, then bi-weekly.
4. Symptom and psychological evaluation every three weeks for six months by the palliative care team.
5. Outpatient palliative care consultations according to a palliative care plan tailored to the patient's needs.
6. Symptom assessment every three weeks via MDASI and PHQ-2.
7. Control group: Usual oncological care with optional usual palliative care.

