## **Data Analysis**

- 1) Survival analysis for two years post-enrollment using Kaplan-Meier curves.
- 2) Mean observed changes from baseline, adjusted differences in change scores at 12, 18, and 24 weeks were analyzed for survivors.
- 3) Effect sizes determined by standardized mean differences (Cohen's d), considering  $\geq 0.3$  as clinically relevant.

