|  |                                          |                                                                                                                                                                                                                                                                                                                                                                          |
|--|------------------------------------------|--------------------------------------------------------------------------------------------------------------------------------------------------------------------------------------------------------------------------------------------------------------------------------------------------------------------------------------------------------------------------|
|  |                                          | 
schedule. (In-person examination is conducted based on the Global Assessment Form and Summary Evaluation Form filled out prior to the examination.)
 
The CRC (or PCT nurse) conducts surveys at weeks 12, 18, and 24. After examination, the Global Assessment Form, Summary Evaluation Form, and Service Log are uploaded to PCT Web.
        |
|  | ▼                                        |                                                                                                                                                                                                                                                                                                                                                                          |
|  | 2. Telephone coaching                    | 
A nurse who completed coaching training conducts telephone counseling weekly from week 1 through week 12, and bi-weekly from week 13 through week 24, using the counseling workbook to manage symptoms and assess the need for crisis intervention. A coaching log entry is made on the website for the palliative care patient management program.
 |
|  | ▼                                        |                                                                                                                                                                                                                                                                                                                                                                          |

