|  | 3. Handover to the existing hospice team | 
If patients advance to an end stage and palliative care is the only treatment option, they are handed over to the conventional hospice team at the hospital and intervention is terminated. Although the intervention for early palliative care is terminated, follow-up surveys continue to be administered.
                                       |
|  |                                          |                                                                                                                                                                                                                                                                                                                                                                          |

|  |                              |                                                                                                                                                                                                         |
|--|------------------------------|---------------------------------------------------------------------------------------------------------------------------------------------------------------------------------------------------------|
|  | Visit at week 24             | Upon completion of the week-24 survey , the study is completed.                                                                                                                                  |
|  | In the case of patient death | 
If a patient dies, the Study Termination Form is filled out.
 
At 3 months after patient death, the family is contacted by phone to administer the 3-Month Post-Death Survey.
 |

*(Recommendations)*

|             |                        |                                                                                                                                                                                                                                                                                                                                                                                                                      |

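### Splitting survival from enrollment by fewer than 10 versus more than 10 interventions favours the high-contact group even if contacts have no effect on survival

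*Protocol*

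**What the plan says.** Protocol, Measurement and statistical analysis, 4) Statistical analysis, makes two-year survival the main survival outcome. It compares the randomised groups by Kaplan-Meier curves and then adds a second comparison. Its purpose is stated: "To determine if the survival rate was higher in the group that received more interventions". Its method is stated too: "participants were divided into groups with fewer than 10 interventions and more than 10 interventions".

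The clock starts at enrollment. The same section says: "Patients who were alive at the time of the last follow-up (two years from the enrollment date) were censored on that date". The Data Analysis list in the overview agrees: "Survival analysis for two years post-enrollment using Kaplan-Meier curves". Neither place mentions a landmark or an exposure that changes with time.

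The interventions come after enrollment. Under 2) Measurement procedure – Intervention Group, telephone coaching runs "weekly from week 1 through week 12, and bi-weekly from week 13 through week 24". The Intervention list in the overview adds "Symptom and psychological evaluation every three weeks for six months by the palliative care team". Delivery ends early for patients who decline: once palliative care is the only option, "they are handed over to the conventional hospice team at the hospital and intervention is terminated". Section 8) Termination of service lists death and this same situation among the reasons for ending service.

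**The concern.** The grouping variable is a count that only time alive can build up, yet survival is measured from before the count begins. Time lived while reaching the eleventh contact is credited to the high group, and nobody who dies in that time can belong to it. Those deaths go to the low group, whatever the contacts do. The handover rule works in the same direction, because deterioration itself halts the count.

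Early deaths should not be rare here. Inclusion criterion 4 reads "Estimated life expectancy of" at most 12 months. The bullet is phrased as a question about benefit and carries no exploratory label, so a positive result could be reported as a dose-response effect of palliative care on survival.

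**Working it through.** The protocol gives no expected survival, attendance or sample size, so there is no figure of its own to reproduce. The check has three parts.

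**1. When can the eleventh contact occur?** Calls: 12 weekly + 6 bi-weekly = 18. Three-weekly visits over 24 weeks: 24 / 3 = 8. Total 18 + 8 = 26. At full attendance:

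- Calls only: week 11.
- Calls plus visits at weeks 3, 6, 9: by week 8 there are 8 + 2 = 10 contacts, so the eleventh falls in week 9.
- Calls plus visits at weeks 1, 4, 7: by week 8 there are 8 + 3 = 11, so week 8. A week-1 visit is possible because the first meeting may take place any time within three weeks of randomization.
- Calls plus two-weekly visits (allowed under Follow-up) at weeks 1, 3, 5, 7: by week 7 there are 7 + 4 = 11, so week 7.

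Entry to the high group thus requires survival of about 7 to 11 weeks, and longer with missed contacts.

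**2. Direct arithmetic at full attendance, no effect of contacts.** Assume exponential survival with a 12-month median: S(t) = 0.5^(t/52), t in weeks. True two-year survival is S(104) = 0.25 for everyone.

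- Calls only: S(11) = 0.5^(11/52) = 0.864. High group: 0.25 / 0.864 = 28.9%.
- Calls plus visits from week 3: S(9) = 0.5^(9/52) = 0.887. High group: 0.25 / 0.887 = 28.2%.
- Low group: 0% in both cases, because only patients who died early can be in it.

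**3. Simulation under the null with missed contacts.** Survival is exponential. Attendance varies between patients (beta-distributed) and is unrelated to prognosis. Contacts stop at death unless stated, and follow-up is censored at 104 weeks. There are 200,000 EPC patients per scenario. All survival and attendance values are assumptions. Results for a 12-month median (truth: 25% in both groups, hazard ratio [HR] 1), shown as two-year survival for >10 vs <10:

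| Mean attendance | Calls only | Calls plus visits |
|---|---|---|
| 90% | 29% vs 4.5%, HR 0.15 | 29% vs 1%, HR 0.06 |
| 80% | 30% vs 10%, HR 0.31 | 29% vs 4%, HR 0.15 |
| 70% | 31% vs 15%, HR 0.45 | 29.5% vs 9%, HR 0.29 |
| 70%, Beta(7,3) | 31% vs 13%, HR 0.39 | 30% vs 5%, HR 0.16 |

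The last two rows share a mean and differ in the spread of attendance between patients, so spread matters as well as the mean. Other settings:

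- 70% with a wide spread, Beta(1.4, 0.6): HR about 0.44 to 0.54 (calls only) and 0.39 to 0.47 (calls plus visits).
- 50%, Beta(5,5): HR about 0.52 to 0.65 and 0.39 to 0.49. The weakest bias is calls only with an 18-month median.
- Contacts stopping 4 weeks before death (assumed lead): bias increases, for example HR 0.31 becomes 0.26.
- Controls pooled into the low group: HR 0.53 to 0.79.
- False-positive rate of a two-sided 5% log-rank test with 50 to 100 EPC patients (assumed), median 9 or 12 months, attendance 70% to 90%: 65% to 100%.

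**Same null after a week-24 landmark.** HR is 0.95 to 1.03 if contacts stop only at death, and 0.89 to 0.99 if they stop 4 weeks before. At 100% attendance nobody alive at week 24 has fewer than 10 contacts. At 90% the low group is roughly 0.6% to 3% of survivors, and the log-rank test is unstable.

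**The case against.** The strongest reply is about weight and size. The primary outcome is 24-week quality of life, survival is not among the secondary outcomes listed under Measures, and this split is one bullet. An unseen statistical analysis plan might add a landmark. The count may also include crisis contacts, which go to sicker patients: in an assumed sketch with 2 to 6 extra contacts in the last 12 weeks of life, the calls-only HR moved from 0.40 to between 0.48 and 0.60.

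Part of this stands. The size is not knowable from the documents, and it shrinks with poor attendance unrelated to prognosis, with crisis contacts counted, or with controls pooled. None of these removed the bias in any scenario tried. The analysis-plan argument does not rescue the text, because the protocol itself fixes the split, its purpose and the time origin.

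Some stronger readings are tempting and should not be drawn:

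- *That the analysis finds a benefit whatever the truth.* Only the null was examined, not a harmful effect, and the false-positive rate was 65% to 100%, not always 100%.
- *That a particular very small HR is what this trial would see.* That rests on one assumed attendance pattern and on counting EPC patients only.
- *That handover marks imminent death.* The protocol gives no interval from handover to death; any lead time is assumed.
- *That the survival results as a whole are compromised.* The EPC-versus-control comparison uses the randomised groups and is untouched.

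The unassigned patients with exactly 10 contacts and the undefined term for interventions are details that an analysis plan could settle. They add no weight here.

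**Conclusion.** The comparison is wrong as written. Its direction follows from the protocol's own rules: a post-enrollment count, a clock starting at enrollment, and delivery that stops at death or handover. Under no effect, the HR within the EPC arm runs from near 0 to about 0.65 for assumed medians of 6 to 18 months and mean attendance of 50% to 90%, and is about 0.5 to 0.8 with controls pooled. These figures rest on exponential survival and on attendance independent of prognosis. Attendance linked to better health would add confounding in the same direction. The flaw is confined to this one dose-response comparison.

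**What to change.** Replace the bullet along these lines:

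- Restrict the comparison to the EPC arm and state which contacts count.
- Enter the cumulative contact count as a time-dependent covariate, so that each patient's time counts as low exposure until the eleventh contact has taken place. Alternatively, use a landmark: among patients alive at the chosen week, classify by contacts received up to then (10 or fewer versus more than 10, or a cut suited to that week) and count survival from that week.
- Label the result exploratory and non-causal, since handover to hospice still confounds it under either method.
- Draw survival conclusions only from the randomised comparison.

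The cost is one paragraph of text and one re-run on data already collected; the time-dependent model also needs contact dates, which the coaching and service logs should supply. A landmark loses patients who die before it, and at week 24 the low-contact group may be nearly empty if attendance is high. The time-dependent model or an earlier landmark may therefore be needed.

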## Detailed study procedure

### 1) Study registration and random assignment

| Task |                    | Actor              | Details                                                                                                                                                                                                                                                                                                                                                                                                                                                                                                                                                                                                                                                                                                                                                                                                                                                                                                                                                                                                                                                                                                                                                                                                                                                                             | Relevant Forms                                                |
|------|--------------------|--------------------|-------------------------------------------------------------------------------------------------------------------------------------------------------------------------------------------------------------------------------------------------------------------------------------------------------------------------------------------------------------------------------------------------------------------------------------------------------------------------------------------------------------------------------------------------------------------------------------------------------------------------------------------------------------------------------------------------------------------------------------------------------------------------------------------------------------------------------------------------------------------------------------------------------------------------------------------------------------------------------------------------------------------------------------------------------------------------------------------------------------------------------------------------------------------------------------------------------------------------------------------------------------------------------------|---------------------------------------------------------------|
| 1    | Study introduction | Primary oncologist | 
 
■ Screen outpatients and inpatients on the inclusion and exclusion criteria.
 
■ Inform the patients who satisfy all inclusion criteria and do not meet any of the exclusion criteria, and their families, of the study in detail.
 
■ Instruct patients and their families who agree to participate in the study to sign a written consent form.
 
 
※ If the family did not accompany the patient to the hospital or does not wish to participate in the study, the patient can register for the study alone. However, if a patient refuses to participate, neither the patient nor the family can register.
 
※ For future analysis, patients' resident registration numbers will be collected and their consent on the utilization of the information will be obtained. The information will be used to make inquiries about patient deaths at Statistics Korea and to link to National Health Insurance Corporation databases to examine the rate of hospice care center utilization and conduct analyses on medical expenditure.
 
 
■ Study subjects are either instructed to contact CRC directly or guided to the palliative care outpatient clinic.
 
 | Study Description and Consent Form                            |
| 2    | Referral           | Primary oncologist | 
 
■ At the time of referral, record the following information: (recommendation)               
 
- Primary diagnosis (cancer type), purpose of the referral, current anticancer therapy, treatment plan if the current therapy fails
 
 
 
                                                                                                                                                                                                                                                                                                                                                                                                                                                                                                                                                                                                                                                                                                                                                                                                                                                                                                                                         | Palliative Care Patient Management Program
- Referral Form |
| 3    | Initial survey     | CRC/PCT nurse      | 
 
■ Administer the baseline survey.
 
                                                                                                                                                                                                                                                                                                                                                                                                                                                                                                                                                                                                                                                                                                                                                                                                                                                                                                                                                                                                                                                                                                                                                                                                 | Baseline Survey                                               |

|   |                                                                                                   |               |                                                                                                                                                                                                                                                                                                                                                                                                                                                                                                                                                                                                                                                                                                                                                                                                                                                                                                                                              |                                                                                 |
|---|---------------------------------------------------------------------------------------------------|---------------|----------------------------------------------------------------------------------------------------------------------------------------------------------------------------------------------------------------------------------------------------------------------------------------------------------------------------------------------------------------------------------------------------------------------------------------------------------------------------------------------------------------------------------------------------------------------------------------------------------------------------------------------------------------------------------------------------------------------------------------------------------------------------------------------------------------------------------------------------------------------------------------------------------------------------------------------|---------------------------------------------------------------------------------|
| 4 | Random assignment                                                                                 | CRC/PCT nurse | 
 
■ Connect to iCReaT to register patients and perform random assignments. 
 
- Random assignment within an age group (<65 or ≥65)
 
 
 
                                                                                                                                                                                                                                                                                                                                                                                                                                                                                                                                                                                                                                                                                                        | iCReaT                                                                          |
| 5 | Description of services to be provided                                                            | CRC/PCT nurse | 
 
■ Describe to patients the services they will receive. 
 
- Intervention Group: Inform patients of the following: follow-up at weeks 12, 18, and 24; PCT examination approximately once every 3 weeks; and telephone coaching (weekly from week 1 through week 12 and bi-weekly from week 13 through week 24. Provide patients with copies of the workbook and the execution planner, and educational materials and CDs for early palliative care and advance care planning.
 
- Comparison Group: Inform patients of follow-up at weeks 12, 18, and 24, and provide them with educational materials and a CD on cancer pain management.
※ If patients in Comparison Group wish to receive palliative care, make an arrangement so that they may receive the existing conventional palliative care provided by the institution.
 
 
 
 |                                                                                 |
| 6 | 
(For Intervention Group)
 
Early palliative care registration and baseline assessment
 | CRC/PCT nurse | 
 
■ After patient registration, summarize the results and fill out the Basic Patient Registration Form.
 
                                                                                                                                                                                                                                                                                                                                                                                                                                                                                                                                                                                                                                                                                                                                                                                      | Palliative Care Patient Management Program
- Basic Patient Registration Form |
| 7 | 
(For Intervention Group)
 
Scheduling appointments
                                    | CRC/PCT nurse | 
 
■ Schedule the next appointment for outpatient examination by a palliative care specialist on next hospital visit (or on a day of patient choice).
 
                                                                                                                                                                                                                                                                                                                                                                                                                                                                                                                                                                                                                                                                                                                                         |                                                                                 |
| 8 | Compensation Payment                                                                              | CRC/PCT nurse | 
 
■ Ask patients to sign the Compensation Payment Form for their assigned group.
※After patients sign the form, send the form to the appropriate personnel at Seoul
 
                                                                                                                                                                                                                                                                                                                                                                                                                                                                                                                                                                                                                                                                                                                      |                                                                                 |

|  |  |  |                      |  |
|--|--|--|----------------------|--|
|  |  |  | University Hospital. |  |
|--|--|--|----------------------|--|

